### Participant timeline {13}

The flow of participants through the present RCT is presented in Fig. 2.

**Fig. 2 Fig2:**
[figure not shown]
Flow diagram showing the steps participants take in the RCT

### Sample size {14}

Sample size was based on detecting non-inferiority of telerehabilitation circuit training in comparison to the face-to-face method at 14 weeks after randomization, considering the primary outcomes pain (VAS) and disability (WOMAC function sub-scale). For change in VAS, a non-inferiority margin (NIM) of 16 mm was chosen as this is less than the minimum clinically important difference (MCID) of 17.5 mm from a 100-mm VAS for OA patients [55]. For change in WOMAC function sub-scale, a NIM of 7.5 units (11% of scored 0–68) was chosen as this is less than the MCID of 12% (8.16) of improvement from baseline in OA research [56]. Assuming standard deviations (SD) for changes from baseline of 17.9 mm and 12.12 units for pain intensity and physical function respectively [10, 25], 80% power and a one-sided 2.5% significance level, we needed 20 people per arm for change in pain intensity and 41 people per arm for change in physical function. However, considering 18% loss to follow-up, we needed 25 and 50 people per arm for change in pain intensity and physical function, respectively. Thus, a total of 100 people will be included in the trial. No adjustments for multiplicity was made. Sample size calculation was performed using the software G*Power, version 3.1.

### Recruitment {15}

Participants from the community of São Carlos, Brazil, will be recruited by ads in local newspapers, magazines and social media.

## Assignment of interventions: allocation

### Sequence generation {16a}

Participants will be randomly assigned to the intervention group through the stratified randomization method. This method can be used to achieve balance among groups in terms of participants’ baseline characteristics. Thus, participants will be paired into two groups (allocation 1:1) considering similar baseline characteristics, such as sex, age, BMI, and knee OA grade. Once paired, a simple randomization will be performed through a randomization site (http://www.random.org/) to define the intervention method of each group (TR and FtF).

### Concealment mechanism {16b}

A single investigator, who will have access only to participants’ baseline characteristics, such as sex, age, BMI, and knee OA grade, will be responsible to pair participants as explained under sequence generation section. Then, the same investigator will perform a simple randomization through a website which will decide the intervention received by each participant (TR of FtF). The investigator will inform both the participants and physical therapist responsible to interventions.

### Implementation {16c}

All patients who give consent for participation and who fulfill the inclusion criteria will be randomized. Randomization will be requested by the Trial Coordinator after conclusion of the baseline assessments and after pairing participants (1:1). The estimated time between baseline assessments and allocation will not exceed 7 days. To make RCT feasible, the study sample will be divided into three stages: the first stage will recruit 20 participants (10 per arm), and the second and third stages will recruit 40 participants each (20 per arm), totaling 100 participants.

## Assignment of interventions: blinding

### Who will be blinded {17a}

The outcome assessors and the data analysts will be blinded to the treatment groups. Due to the nature of the interventions, it will not be possible to blind neither the patients nor the physical therapist responsible to interventions. Thus, it is important to note that the primary outcomes (pain intensity, VAS; and disability, WOMAC function sub-scale), as well as pain catastrophizing, adherence, acceptability and treatment perspective are patient reported, and hence they cannot be blinded.

### Procedure for unblinding {17b}

The trial design is a single-blinded study; thus, only the outcome assessors and the data analysts will be blinded. Thus, there is no unblinding procedure foreseen.

## Data collection and management

### Plans for assessment and collection of outcomes {18a}

Assessments will be conducted face-to-face at the Joint Function Analysis Laboratory (LAFAr) and at the University Hospital (UH) of the UFSCar and will be divided into 3 days.

At the first assessment day, participants will undergo a physical therapy evaluation consisting of inspection, palpation, and knee and hip range of movement analysis, as well as tests to assess ligament integrity. Afterwards, an evaluation form will be completed (personal, anthropometric, socioeconomic, medication, blood pressure, knee pain data, and previous medical history). In addition, the body composition exam (dual energy X-ray absorptiometry (DXA)) and the performance-based tests will be held in the same visit. This first day of assessment will be performed by the same physical therapist/researcher and will have a total duration time of approximately one hour.

The second assessment day will be scheduled at least 2 days after the first assessment. In this visit, the WOMAC questionnaire, the Pain Catastrophizing Scale (PCS) and the Visual Analog Scale (VAS) will be participant-reported on a paper form. Then, participants will undergo an ultrasound evaluation of the thigh vastus lateralis muscle by a previously trained evaluator, blinded to intervention groups. Afterwards, participants will perform the isometric strength test. The second assessment day will also be conducted by the same physical therapist/researcher and will have a total duration time of approximately one hour.

Finally, participants will receive a referral for the thigh computed tomography (CT) scan exam that composes the third assessment day. The CT will be performed at the University Hospital (UH) – UFSCar by an experienced radiologist collaborator of this study. The CT exam has a duration time of approximately 10 min. More detailed information on the data collection for these study outcomes was provided in the “Outcomes {12}” section.

Adherence, acceptability, and treatment perspective will be self-evaluated during the end-points (14 weeks and 26 weeks). Thus, questions related to these outcomes will be included in the first day of assessment post-intervention.

The assessments will be conducted at all timepoints (baseline, 14 weeks, and 26 weeks) by the same physical therapist/researcher. It is important to note that the CT exam will also be performed by the same radiologist. Both physical therapist/researcher and radiologist will be blinded to the intervention’s groups. In addition, all randomized participants will be invited to attend all timepoints of the study, even if they do not adhere to the interventions.

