#### Adherence, acceptability, and treatment perspective

Adherence/acceptability to TR, as proposed by Hinman et al. [32] will be assessed by the number of calls received from the lead investigator, as well as the number of sessions per week the participant performed, which should be self-reported during phone calls. The FtF will be evaluated by the number of sessions that the participant attended. In addition, for the same purpose, questions will be asked such as “Do you agree with the proposed exercise plan?” and “Did you perform the exercise program?” Where 0 refers to “strongly disagree” and 10 “strongly agree”. The participants will also qualitatively evaluate the expectation with the result of the exercise protocol, where the scale may vary from “no effect” to “complete recovery” [32]. These outcomes will be self-reported on a paper form only during end-points (14 weeks and 26 weeks).

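### The adherence and acceptability form is scheduled in the blinded assessor's first post-treatment visit, ahead of that assessor's strength test and of all 26-week tests

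*Protocol article*

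**What the plan says.** The protocol article (Plans for assessment and collection of outcomes {18a}) spreads each assessment over three days. On the first day "the performance-based tests will be held in the same visit" as the body composition scan, and "This first day of assessment will be performed by the same physical therapist/researcher". For timing, "The second assessment day will be scheduled at least 2 days after the first assessment". On day 2, after the questionnaires and the ultrasound, "Afterwards, participants will perform the isometric strength test", and "The second assessment day will also be conducted by the same physical therapist/researcher". Across the trial, "The assessments will be conducted at all timepoints (baseline, 14 weeks, and 26 weeks) by the same physical therapist/researcher". This person is to be blinded to group.

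The adherence, acceptability and treatment-perspective outcomes are collected at 14 and 26 weeks, and "questions related to these outcomes will be included in the first day of assessment post-intervention".

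The section Adherence, acceptability, and treatment perspective defines adherence by arm. In the telerehabilitation (TR) arm it is "assessed by the number of calls received from the lead investigator" together with weekly sessions reported by telephone. In the face-to-face (FtF) arm it is the number of sessions attended. The section then adds two 0–10 questions, on agreement with the plan and on having done the programme, and a scale for the expected result. It closes by saying that these outcomes are self-reported on paper at the two end-points.

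**The concern.** Participants and treating therapists know the allocation. For walking speed, chair stands, stair time and isometric torque, the main protection against a biased reading is that the person giving instructions and encouragement does not know the arm. These tests depend on effort, and the torque test is done with standardised verbal encouragement.

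How, where and whether a participant exercised is the subject most likely to disclose the arm. The plan places it in a visit run by the one person who must not know. Because the same person assesses at every time point, a disclosure at 14 weeks cannot be undone at 26 weeks. What is at stake is the credibility of the assessor-run secondary outcomes, not the primary non-inferiority conclusion.

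**Working it through.** No figure in the protocol bears on this point, so the check is of sequence, content and handling.

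**1. Sequence.** There are four assessor-run, effort-dependent tests per time point: three performance tests on day 1 (40 m walk, 30-second chair stand, stair climb) and isometric torque on day 2. Over the two post-treatment time points that makes 4 × 2 = 8.

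| Test | Position relative to the 14-week form |
|---|---|
| 14 weeks, three performance tests (day 1) | Same visit; order not stated |
| 14 weeks, torque (day 2) | After it, by at least 2 days |
| 26 weeks, three performance tests | After it |
| 26 weeks, torque | After it |

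So 1 + 3 + 1 = 5 of the 8 tests certainly follow a completed form. The other 3 may or may not.

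**2. Content.** The items named in the adherence section fall into two kinds.
- Neutral between arms: agreement with the plan, having done the programme, and the expectation scale.
- Specific to an arm: number of calls received and home sessions (TR), and number of supervised sessions attended (FtF).

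The section is not clear on whether the second kind is on the form. TR sessions are to be reported during the calls, yet the closing sentence puts these outcomes, without exception, on the end-point paper form. Arm-revealing items are therefore possible, not established.

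**3. Handling.** The form is completed by the participant. The article does not say that the assessor asks, reads or receives the answers. It does fix the visit, and the assessor runs that visit.

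**4. Reach.** Under Implementation {16c}, stages 1 to 3 recruit 20, 40 and 40 participants. Under Trial status, the first two blocks are complete (20 + 40 = 60) and the last 40 participants have not started.

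**The case against.** The strongest reply is that this infers a breach from silence. The article requires a blinded assessor in several places and states nothing that contradicts it. The form is self-completed, its quoted questions read the same in both arms, and TR session counts are already taken by telephone. The order of forms and the use of envelopes are normally left to the full protocol or to working procedures. An unblinded participant could also mention the arm at any visit, so the form is only one channel.

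Most of this stands, and it limits the point. A reader might infer three stronger things that the document does not support:
- That the assessor collects the answers. The article says only that participants report them on paper.
- That the assessor learns the arm before the 14-week walk, chair-stand and stair tests. No order within day 1 is given.
- That assessor blinding is the trial's only blinding of outcomes. The data analyst, the staff who enter and check data, the reader of the thigh CT and the reviewer of the ultrasound images are blinded too, and nothing in the plan ties the readings of those images to the day-1 form.

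The reply does not remove the scheduling itself. The article does not leave the day open. It assigns the form to day 1, when a position after the day-2 strength test was available at no cost. That other routes to disclosure exist is no reason to keep one that can be closed.

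**Conclusion.** The point holds as an avoidable risk to assessor blinding, not as a demonstrated loss of it. It is certain in sequence for isometric strength at 14 weeks and for all four assessor-run tests at 26 weeks. It is only possible for the three performance tests at 14 weeks.

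It rests on two assumptions that the article neither confirms nor excludes: that the form, or talk prompted by it, can reveal the arm, and that the assessor can see or hear it. The size and direction of any bias cannot be derived from the document. Pain on the VAS and WOMAC function are reported by unblinded participants in any case and are not affected, so the non-inferiority result does not depend on this. The change is worth making because it costs almost nothing and protects several secondary outcomes.

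**What to change.** For all 14- and 26-week visits still to come, which are mainly those of the final 40 participants:
- Give the adherence, acceptability and treatment-perspective form after the last assessor-run test on day 2.
- Have the participant return it sealed to staff other than the assessor, for example the Trial Coordinator.
- Take call counts and session counts from the therapist's call records and the attendance logs, so that neither passes through the assessor.
- Clarify in the adherence section which items are on the paper form and which come from these records.

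For the 60 participants in the two completed blocks, state in the results report when the form was completed relative to the tests and who handled it.

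The cost is a small change in the order of forms, with no extra visit, staff or participants. The limit is that the completed blocks cannot be protected after the fact. The form's timing will also differ by at least two days between the earlier blocks and the last one, which should be noted in the report.

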### Plans to promote participant retention and complete follow-up {18b}

Participants will receive extensive information about the study design and requirements during the recruitment. The importance of the follow-up completion will be informed. Participants are allowed to withdraw from the study at any time and for any reason without penalty. However, if possible, participants will be invited to attend the end-point assessment of the present study (14 weeks and 26 weeks).

### Data management {19}

After checking for completeness, the data will be entered in an electronic password-accessible database by a blinded collaborator of this study. In a separate step, the correct transfer and coding of the data will be checked by a different blinded collaborator. All research data will be archived for 10 years after the study has ended according to the local ethics committee.

### Confidentiality {27}

The present study data will be documented and archived using an identification code for each participant. All personal information will be stored in a locked, password-accessible database. Paper forms and exams report containing personal information will be locked in a lockable metal cabinet. Physical and electronic personal documents will be safeguarded by the Trial Coordinator for 10 years as recommended by the local ethics committee; after that, they will be destroyed and deleted.

### Plans for collection, laboratory evaluation, and storage of biological specimens for genetic or molecular analysis in this trial/future use {33}

No biological specimens will be collected.

## Statistical methods

### Statistical methods for primary and secondary outcomes {20a}

A blinded data analyst will perform all analysis using the Statistical Package for Social Science, version 20.0 (SPSS Inc, Chicago, IL, USA). Baseline characteristics of participants will be presented using descriptive statistics. The between-group differences and 95% confidence interval (CI) for the post-treatment outcomes at 14-week and 26-week end-points will be calculated using mixed linear models using interaction terms of treatment group versus time with no covariate adjustment. Non-inferiority will be demonstrated if the lower bound of the two-sides 95% CI for between-group difference (telerehabilitation minus face-to-face) is above −16 mm in pain intensity and/ or −7.5 units for change in WOMAC physical function subscale at 14 weeks after randomization. Multiple imputation method will be used to impute missing data by using the multiple imputations function in SPSS [57], and an intention-to-treat analysis [58] (including all randomized participants) will be conducted. No adjustments for multiplicity will be made.

It is important to note that, if appropriate, a full statistical plan will be finalized prior to analysis.

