#### Intervention description {11a}

##### Face-to-face (FtF) circuit protocol

Participants allocated to this group will attend all of their exercise sessions supervised by a trained physical therapist in the Federal University of São Carlos (UFSCar).

The exercise protocol will be performed in a group of up to 5 participants, three times a week, for 14 weeks, totaling 42 sessions [7]. Each session will consist of 5 min of warm-up (stationary bike or walk), circuit protocol, and 5 min of stretching exercises (cool down). Immediately after the warm-up, participants will begin the circuit protocol consisting of exercises for the upper limbs, lower limbs, trunk, and global exercises.

Participants will be instructed to perform each exercise as fast as possible, with the maximum number of repetitions during the time set for the training phase (light, moderate, or intense), in order to ensure the aerobic component [7]. After the first exercise, the participant should move to another station, following a specific order and allowing different muscle groups to alternate between rest and work, favoring recovery and minimizing the risk of muscle fatigue [7].

During the first week of exercise, participants will be familiarized with the equipment and exercises that will be performed during the protocol, performing stratified light exercises, where each exercise should be performed for only 10 s [7]. In the second, third and fifth weeks of training, participants will also perform exercises stratified as light, but each exercise will last 20 s. Moderate exercises will be performed in the sixth, eighth, and ninth weeks, lasting 30 s each. Intense exercises will be performed in the eleventh, twelfth, and fourteenth weeks, lasting 40 s each. The fourth, seventh, tenth, and thirteenth weeks will be considered as regenerative weeks, during which light exercises will be performed for a shorter time (10 s). For all intensities, a maximum transition interval of 30 s between stations will be implemented [7].

The exercises that compound each of the circuit training phases, as well as the execution time are presented in Additional file 1.

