##### Telerehabilitation (TR) circuit protocol

Participants allocated to the TR group will be invited to attend the Department of Physical Therapy at UFSCar after randomization and before starting the intervention. This visit will be held individually so that the participant has full attention from the physical therapist to clarify questions, possible adaptations regarding the execution of exercises at home, as well as signs and symptoms to interrupt the session. In addition, during this visit, participants will receive a DVD with recordings of the circuit exercise sessions, the material needed to perform all the exercises, and a diary to record the days that they will perform the exercises. The materials provided to the participants are the same used in the FtF group and include a pair of 0.5-kg dumbbell, a pair of 1.0-kg dumbbell, a light elastic band, a hard-elastic band, a small ball, a 0.5-kg ankle weight, and a 1.0-kg ankle weight.

The TR group exercises will follow the same model proposed for the FtF group, following the same progression, execution time, and rest time (Additional file 1). However, these participants will perform the exercise sessions remotely.

Participants from this group will be instructed to perform the exercises scheduled for this week following the instructions given via DVD, website (http://exercicio-joelho.trekeducation.org), *YouTube* channel (http://bit.ly/telereabufscar), and/or videos via *WhatsApp*. The exercises should be performed three times weekly, preferably on non-consecutive days. Each session will consist of 5-min warm-up (light walking, steady walking), circuit exercises, and cool-down (5-min stretching), identical to the FtF group.

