## Trial status

The protocol was registered on 31 March 2019, under the registration RBR-662hn2. The first two blocks of recruitment, allocation and analysis have already been completed. However, the final block of participants (*n* = 40) did not start yet due to the delay caused by the COVID-19 pandemic. Data recruitment began: 01 April 2019. Data when recruitment will be completed: 30 July 2021 - Version 2 (recruitment date updated - under review).

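### The primary model excludes all covariates: this loses precision on WOMAC function, and the omitted pairing factors and face-to-face classes pull the interval in opposite directions

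*Protocol article*

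**What the plan says.** All references are to the protocol article.

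- **Analysis** (Statistical methods for primary and secondary outcomes {20a}): the differences and 95% intervals at 14 and 26 weeks "will be calculated using mixed linear models using interaction terms of treatment group versus time with no covariate adjustment". The section describes these as differences in post-treatment outcomes, but words the WOMAC non-inferiority rule in terms of change. A full statistical plan is promised only conditionally.
- **Allocation** (Sequence generation {16a}): "participants will be paired into two groups (allocation 1:1) considering similar baseline characteristics, such as sex, age, BMI, and knee OA grade", followed by simple randomisation.
- **Stages** (Implementation {16c}): "the first stage will recruit 20 participants (10 per arm), and the second and third stages will recruit 40 participants each (20 per arm"). Trial status reports two stages done and says that the last 40 participants "did not start yet due to the delay caused by the COVID-19 pandemic".
- **Sample size** {14}: "Assuming standard deviations (SD) for changes from baseline of 17.9 mm and 12.12 units", with margins of 16 mm and 7.5 units.
- **Delivery**: in the face-to-face (FtF) arm, "The exercise protocol will be performed in a group of up to 5 participants". In the telerehabilitation (TR) arm, "these participants will perform the exercise sessions remotely".
- **Measurements** (Plans for assessment and collection of outcomes {18a}): VAS and WOMAC are recorded at baseline, 14 and 26 weeks.

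Neither the sample-size section nor the analysis section mentions pairs, stages or classes.

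**The concern.** Non-inferiority is decided by one confidence limit, so the standard error matters directly. The plan excludes covariates by statement, not by silence, and a later analysis plan that added them would contradict this text. There are three separate consequences.

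1. **Baseline score.** It is normally the strongest predictor of the follow-up score and is already collected. WOMAC function sets the sample size and has no power to spare.
2. **Pairing factors and stage.** Allocation is deliberately balanced on them. A model that omits them does not credit that balance and overstates the standard error.
3. **FtF classes.** Participants who share a class and a therapist may have correlated outcomes, and TR has no classes. A model that treats everyone as independent understates the standard error, which for non-inferiority is the lenient direction.

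The wording also leaves unclear whether the contrast is in post-treatment scores or in change. Only the latter matches the SDs used for sizing.

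**Working it through.** **Plan's own figures.** n per arm = 2 × [SD × (1.960 + 0.842) / margin]², with a true difference of 0, one-sided 2.5% and 80% power.
- VAS: 2 × (17.9 × 2.802 / 16)² = 19.6, so 20.
- WOMAC function: 2 × (12.12 × 2.802 / 7.5)² = 40.99, so 41.
- After 18% loss: 20 / 0.82 = 24.4, so 25; 41 / 0.82 = 50.

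The stated sizes reproduce. At 41 per arm, function has 80.0% power by the normal formula and 79% by the noncentral t used below. VAS has 98%, so what follows matters mainly for function.

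**Baseline as covariate.** Let r be the correlation between baseline and 14-week scores, with equal variance s² at both times. The documents give no r; 0.3 to 0.7 is assumed. Change-score variance is 2s²(1 − r) and baseline-adjusted variance is s²(1 − r²), so the ratio is (1 + r)/2. The variance of an unadjusted post-score contrast, relative to change, is 1/[2(1 − r)].

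| r | Adjusted / change variance | Interval width ratio | Power, adjusted | Post-score / change variance | Power, unadjusted post-score |
|---|---|---|---|---|---|
| 0.3 | 0.65 | 0.81 | 93% | 0.71 | 91% |
| 0.5 | 0.75 | 0.87 | 89% | 1.00 | 79% |
| 0.7 | 0.85 | 0.92 | 85% | 1.67 | 57% |

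Power is for function: margin 7.5, change SD 12.12, 41 per arm. The change-score contrast has 79% at every r, because its SD is the planning input. With baseline in the model, the group effect is the same whether the response is the post score or the change, so the ambiguity in wording disappears.

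**Pairing factors omitted.** Let R² be the share of outcome variance that the balanced factors explain (assumed 0.05 to 0.20). The true variance is (1 − R²) times the model's, and the true one-sided error is 1 − Φ(1.96/√(1 − R²)).
- R² 0.05: interval 1.03 times too wide, error 2.2%.
- R² 0.10: 1.05 times, 1.9%.
- R² 0.20: 1.12 times, 1.4%.

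**FtF classes omitted.** For classes of m in one arm, the design effect there is 1 + (m − 1) × ICC, and the variance of the difference rises by 1 + (m − 1) × ICC/2. The documents give no ICC; 0.02 to 0.10 is assumed. With m = 5:
- ICC 0.02: variance × 1.04, SE × 1.02, one-sided error 2.7%.
- ICC 0.05: × 1.10, SE × 1.05, 3.1%.
- ICC 0.10: × 1.20, SE × 1.10, 3.7%.

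Five is a maximum. With classes of 4, ICC 0.02 and 0.05 give 2.7% and 2.9%; with classes of 3, 2.6% and 2.8%.

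**Both together.** The ratio of true to model variance is 1 − R² + 2 × ICC for m = 5. At R² 0.10 with ICC 0.05 it is 1 − 0.10 + 0.10 = 1.00, so the effects cancel. They also cancel at R² 0.20 with ICC 0.10. Over R² 0 to 0.20 and ICC 0 to 0.10, the SE ratio runs from √0.80 = 0.89 to √1.20 = 1.10, and the one-sided error from 1.4% to 3.7%.

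**The case against.** A reader might infer that the confidence intervals are simply wrong, or that baseline imbalance biases the decisive limit. The documents do not support either reading.

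- **Baseline may not be discarded.** In a group-by-time model, baseline can be one of the time levels. The interaction then estimates the difference in change, which matches the planned SD. Under that reading the trial has the power it claims.
- **Chance imbalance is not bias.** In a randomised comparison it is sampling variation that the standard error already carries. Omitting baseline is inefficient, not invalid.
- **The 57% power figure is one end of a range.** It needs both the post-score reading and r = 0.7; the same reading gives 91% at r = 0.3.
- **Stage does not confound.** It is balanced by arm (10, 20 and 20), so omitting it affects only the standard error.
- **The class effect is uncertain and modest.** It rests on an assumed ICC and on full classes. Ruling out covariates does not strictly rule out a class random effect, and random-effects structure is often left to an analysis plan. About ten classes (50 / 5) would estimate a class variance poorly.
- **Timing.** Trial status says analysis of the first two stages (60 of 100 participants) is complete, so the change would be made mid-trial.

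All of this stands except that timing does not defeat the remedy: 40 participants are still to be recruited, and a dated amendment can precede the final analysis. The class effect belongs in a sensitivity analysis, not in the primary model.

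**Conclusion.** The point holds as one of efficiency and of fit between design and analysis. Excluding the baseline score gives up a 15% to 35% reduction in variance relative to a change-score contrast. That is the difference between about 79% and 85% to 93% power for WOMAC function, assuming r of 0.7 to 0.3 and equal variances at the two times. It also leaves the contrast open to two readings with different precision. Omitting the pairing factors is conservative, and ignoring the FtF classes is anti-conservative. Each moves the one-sided error by about one percentage point at most over the assumed ranges, and they can cancel. The documents do not show which way the net error goes. No sizing error is shown, and VAS is hardly affected.

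**What to change.** By a dated amendment before the final analysis, replace the exclusion of covariates with the following.

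- **Primary model:** a mixed model for the 14- and 26-week scores, with fixed effects for group, time, group × time, baseline value of the outcome (and its interaction with time), sex, age, BMI, knee OA grade and recruitment stage.
- **Sensitivity 1:** the unadjusted group-by-time model as now written, stating whether baseline is a time level.
- **Sensitivity 2:** the primary model plus a random effect for exercise class in the FtF arm only.

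**Cost.** Baseline scores, pairing factors and stage are already part of the trial's records. The class sensitivity analysis needs the class roster, which the article does not describe, and may widen the interval slightly. The main cost is a documented change to a pre-specified model after two of three stages. The amendment should therefore say what results had been seen when it was made, and the unadjusted result should be reported beside the adjusted one.
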